## ENDPOINT / Termination

PatientID:

1

### Endpoint

Reason for leaving:

-

- Death:

-

- Death related to examinations or complications:

-

☐

Examinations within the protocol

- specify:

☐

Complications to secondary surgery

☐

Complications to radiation

☐

Complications to chemotherapy

Recurrence of colorectal cancer:

-

Date of leaving study:

(dd-mm-yy)

Submit

Save

Cancel

## **Appendix 8**

### **Monitoring committees**

#### **Study monitoring:**

To be appointed by Danish Colorectal Cancer Group  
To be appointed by Swedish Colorectal Society  
To be appointed from UK and the Netherlands

## **Appendix 10**

### **Internet randomisation**

The randomisation will take place over the Internet via a server placed at Aarhus University Hospital, Denmark. The server contains a randomisation programme, which each centre will gain access to via a username and password. When logging on to the randomisation site, each centre must key patient data on all patients, who have given their consent and who fulfil the inclusion criteria for the study. After keying the data, a randomisation code will be provided. The data is encrypted before the information is transmitted over the Internet.

### **The project's database**

A database for the project will be established, and this will also be placed at Aarhus University Hospital, Denmark. The Danish Board of Registry has approved the database. Access to the database can be gained through the project's homepage, by providing a valid username and password. Keying of baseline- and follow-up data will be carried out over the Internet using a standard web-browser, so no programmes need to be installed on the computers located at the centre. A number of validation procedures will be installed in order to ensure a high data quality. There will be sent out reminders of all follow-up visits and examinations, and data from these will also be keyed via the Internet. Each centre will be able to log on to the database via the homepage at any time in order to see descriptive data and number of included patients for own centre as well as for the entire study population. The database will ensure that data is available for statistical analysis immediately after termination of the study.

## Appendix 11

## COLOFOL - Flowchart

[figure not shown]

# COLOFOL – Inclusion and exclusion

## Inclusion criteria:

- Radical surgery (R0-resection) for colorectal adenocarcinoma – with or without adjuvant treatment, and
- Age  $\leq 75$  years, and
- Written informed consent, and
- “Clean colon” verified by perioperative barium enema or colonoscopy last 3 months post-surgery, and
- Tumour stage:II-III ( $T_{any} N_{1-2} M_0$ ,  $T_{3-4} N_{any} M_0$  ,Dukes’ B - C)

## Exclusion criteria:

- A clinical diagnosis of HNPCC (non hereditary polyposis colorectal cancer) or FAP (familial polyposis coli),
- Local resection for colorectal cancer (e.g., TEM-procedure),
- Life-expectancy less than 2 years due to concurrent disease (e.g., cardiac disease, liver cirrhosis),
- Inability to provide informed consent or refusal to do so,
- Inability to comply with the follow-up programme,
- Participation in other clinical trials interfering with the control-programmes – e.g. TRIALS on adjuvant therapy with CT endpoints
- Other or previous cancer (except for non-melanoma skin cancer)

Pre – or postoperative adjuvant chemotherapy and/or radiation therapy is allowed, as long as it is applied with same indications in the two groups.

Endoscopy is permitted, as long as equal in the two groups.

## 2. eStatistical Analysis Plan

### AIM

To conduct a prospective multicenter randomised study comparing total mortality, cancer-specific mortality, recurrence-free survival, economic cost effectiveness, and quality of life (QOL) in patients receiving high-volume follow-up after radical resection for colorectal cancer, compared to patients receiving low-volume follow-up.

### STUDY PROCEDURES

#### *Recruitment and Eligibility*

At each participating center, consecutive patients receiving radical surgery for colorectal cancer will be considered for inclusion. Those who are ineligible or who refuse consent will be followed observationally.

#### *Inclusion criteria*

- Radical surgery (resection) for colorectal adenocarcinoma – with or without adjuvant treatment
- Age less than 75 years
- Provision of written informed consent for participation.
- “Clean colon” verified by perioperative barium enema or colonoscopy performed 3 months post surgery, at the latest
- Tumor stage: T2-T4, Nany, M0 or Dukes’ type B or C
- Pre- or postoperative chemotherapy and/or radiation therapy allowed.

#### *Exclusion criteria*

- Clinical diagnosis of HNPCC or FAP
- Local resection for colorectal cancer (e.g., TEM procedure)
- Life expectancy less than 2 years due to concurrent disease (e.g., cardiac disease, terminal multiple sclerosis, liver cirrhosis)
- Inability to provide informed consent or refusal to do so.
- Inability to comply with the control or intense follow-up programme.
- Participation in other clinical trials interfering with the follow-up programmes

*Informed consent* (written) will be obtained within 30 days after surgery and after the primary tumor classification has been made. Patients refusing to participate will be asked for consent to be followed in an observational analysis, using data on their actual follow-up program and their clinical

course.

### *Randomisation and treatments*

Randomisation will take place by telephone, E-mail (or FAX) from a central randomisation unit located in the offices of the Cochrane Colorectal Cancer Group. Randomisation will be stratified according to tumor stage and clinical centre. Randomisation will be blocked, in variable groups of 4 or 6. The allocation procedure will be concealed to participating care providers.

### *Study Follow-up Regimens*

CEA will be measured on all colorectal cancer patients before surgery or preoperative adjuvant therapy and after the completion of primary treatment. All patients will have a “clean colon” within 3 months perioperatively, and at least one perioperative imaging procedure (Ultrasound, MR, or CT) of the liver and x-ray of the lungs. In both study groups an unlimited number of endoscopies will be allowed. Interval diagnostic evaluation also will be allowed for all subjects presenting symptoms.

#### *1. Low-volume follow-up regimen*

- CEA, multislice CT/ or MRI of the liver and X-ray or CT of the lungs one year after surgery. For rectal cancer with re-established luminal continuity, an MR scan of the pelvis and/or endorectal ultrasound (by a dedicated sonographer) at 6, 12, 18, 24, and 36 months after surgery. For patients with abdominoperineal resection, an MR scan of the pelvis at the same intervals.
- Patients will be instructed to contact their recruitment centre if symptoms of recurrence occur.
- If recurrent disease is suspected, diagnostic measures and treatment used normally in the individual centre will be applied.

#### *2. High-volume follow-up regimen*

- CEA, multislice hepatic CT or MR and/or PET scans at 6, 12, 18, 24, and 36 months. For rectal cancer with re-established luminal continuity, MR scan of the pelvis and/or endorectal ultrasound (by a dedicated sonographer) at 6, 12, 18, 24, and 36 months after surgery. Biopsies should be taken if suspected areas are found. For patients with abdominoperineal resection, MR scan of the pelvis at same intervals.
- Patients will be instructed to contact their reference centre if symptoms of recurrence occur.
- If recurrent disease is suspected, diagnostic measures and treatment used normally in the individual centre will be applied.

*Data to be obtained:* the following data will be obtained on all randomised subjects and those who give consent for observational study:

- Baseline demographic, clinical, and lifestyle factors (date of birth, major chronic illnesses, smoking, alcohol intake, medications, etc).
- Results of all diagnostic evaluations for metastatic disease during the initial evaluation
- Detailed description of initial surgical, adjuvant, and radiation treatment
- Findings from all cancer surveillance tests obtained after diagnosis
- Detailed description of all cancer treatments administered after randomisation
- Quality of life (QOL) assessment by telephone interview at 1, 3 and 5 years after randomisation. A standardised and validated QOL instrument, that takes follow-up regimens into consideration, will be used.

### *Statistical analysis and power*

The primary effect parameter of the study will be total mortality and cancer-specific mortality after 5 years; the secondary endpoint will be time to diagnosis of recurrence (*i.e.*, recurrence-free survival) and quality of life.

Results will be evaluated both on an intention-to-treat basis and on an as-treated (per protocol) basis. Patients who withdraw their informed consent and thus change their follow-up programme will remain in their allocation group in evaluations conducted on an intention-to-treat basis, and will be excluded in evaluations conducted on a per-protocol basis.

Non-randomised patients and patients who withdraw their informed consent will be analysed separately.

On the basis of the results listed in Figure 1 in the protocol, an estimate of 5 years' mortality at 60% and a MIREDF (Minimal Relevant Difference) of 6% seem justified. With a risk of type 1 error at 5% and type 2 error of 15%, about 1,100 patients should be randomised to each group. With an expected dropout rate of about 20%, the planned number of randomised patients should be 2,500. Survival data will be analysed according to the Kaplan-Meier method. Comparisons between groups will be made using the log-rank method. Binominal data will be analysed with Chi-square statistics and continuous data will be analysed with the Mann-Whitney U test.

Level of significance = 5%.

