### **Efficacy parametres**

The primary effect-parameter of the study will be total mortality and cancer-specific mortality after 5 years; the secondary endpoint will be time to diagnosis of recurrence (*i.e.*, recurrence-free survival).

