## **Statistical analysis and power**

Results will be evaluated both on an intention-to-treat basis and on an as-treated (per protocol) basis. Patients who withdraw their informed consent and, thus, change their control-programme remain in their allocation group when evaluated on the intention-to-treat basis, and are excluded when evaluated on the fulfilled protocol basis. Non-randomised patients and patients withdrawing their informed consent will be analysed separately.

On the basis of the results listed in Figure 1, an estimate of 5 years' mortality at 60% and a MIREDF (Minimal Relevant Difference) of 6% seem justified. With a risk of type 1 error at 5% and type 2 error of 15%, about 1,100 patients should be randomised to each group. With an expected dropout rate of about 20%, the planned number of randomised patients should be 2,500.

Survival data will be analysed according to the Kaplan-Meier method and comparison between groups will be performed with the log-rank method. Binominal data will be analysed with Chi-square statistics and continuous data with Mann-Whitney U test.

No interim analyses are planned, as this would stop inclusion for several years.

Level of significance two-sided  $p < 0.05$ .

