### **6) *Analysis of follow-up data***

Trial participants will be followed from the date of radical surgery for colorectal cancer until the date of the analyzed study outcome, date of dropout, date when lost to follow-up, or at 10-year follow-up, whichever comes first.

The Kaplan-Meier method and the log-rank test for between-group comparisons will be used to analyze 10-year overall mortality in the post-trial group participants. The colorectal cancer-specific mortality rates will be calculated using a cumulative incidence function and treating death associated with other causes as competing events. Risk differences in the 10-year overall and colorectal cancer-specific mortality will be calculated with corresponding 95% confidence intervals.

The main analyses will be stratified by cancer stage and will be repeated for the subgroups of patients diagnosed with rectal and colon cancer.

In the first sensitivity analysis, we will repeat the main analyses for trial participants from Denmark and Sweden. The overall and colorectal cancer-specific mortality rates will be compared between the 2 countries.

In a second sensitivity analysis, Cox proportional hazards regression will be used to compute crude and adjusted hazard ratios for overall and colorectal cancer-specific mortality rates. The hazard ratios will be adjusted for age at the time of colorectal cancer surgery; sex; colorectal cancer type; cancer stage; comorbidities including diabetes, cardiovascular disease, pulmonary disease, and cerebrovascular disease; preoperative radiation; adjuvant chemotherapy; and smoking.

The level of significance will be  $P < .05$  with a 2-sided test. Statistical software package SAS (SAS Institute, Inc., Cary, NC, USA) will be used for data management and analyses.

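### Trial SAP: Kaplan-Meier is the only time-to-event estimator although 5-year cancer-specific mortality is a primary parameter, and neither protocol nor trial SAP provides for deaths from other causes

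*Combined protocol and SAP*

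**What the plan says.** The protocol, under Efficacy parametres, states: "The primary effect-parameter of the study will be total mortality and cancer-specific mortality after 5 years". The trial SAP repeats this under Statistical analysis and power: "The primary effect parameter of the study will be total mortality and cancer-specific mortality after 5 years". A protocol amendment of September 2012 adds that 3-year figures for both kinds of mortality will be published as well.

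For the analysis, the protocol says "Survival data will be analysed according to the Kaplan-Meier method and comparison between groups will be performed with the log-rank method", and the trial SAP says "Survival data will be analysed according to the Kaplan-Meier method. Comparisons between groups will be made using the log-rank method". In the trial SAP the only other rule that could touch a mortality endpoint is "Binominal data will be analysed with Chi-square statistics"; the protocol has the same rule. Neither document says which rule governs cancer-specific mortality, how a death from another cause is handled, or whether a competing-risk method is intended.

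The separate post-trial SAP for the 10-year analysis does split the endpoints. In its section 6, overall mortality goes to Kaplan-Meier and log-rank. Colorectal cancer-specific mortality is calculated "using a cumulative incidence function and treating death associated with other causes as competing events", and risk differences with 95% confidence intervals are given for both endpoints.

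**The concern.** A patient who dies of heart disease can no longer die of colorectal cancer. If Kaplan-Meier treats that death as censoring, it behaves as though the patient remained at risk. One minus the curve then estimates cancer mortality in a hypothetical population in which nothing else kills, not the proportion of patients who die of colorectal cancer within 5 years. The error is always upward.

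What is at stake is the reported absolute 5-year cancer mortality in each arm, which is a primary result. Agreement with the 10-year report is also affected. There the same endpoint is a cumulative incidence, so a reader who sets the 5-year figure beside the 10-year one would be comparing two different quantities.

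**Working it through.** **Inputs.** From the documents: 60% 5-year mortality, a 6-point difference, two-sided 5% type 1 error, 15% type 2 error, and about 1,100 patients per group. Assumed, because the documents do not give it: the share q of deaths from other causes, taken from 10% to 50%. Also assumed: constant hazards within each arm.

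**The plan's own figure.** The power statement reads "an estimate of 5 years' mortality at 60% and a MIREDF (Minimal Relevant Difference) of 6% seem justified" and "With a risk of type 1 error at 5% and type 2 error of 15%, about 1,100 patients should be randomised to each group". For a log-rank test (Schoenfeld), events = 4(1.960 + 1.036)² / (ln HR)², with HR = ln(1 − p2)/ln(1 − p1). Events are divided by the mean event probability to give patients.

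- 60% against 66%: HR 1.177, 1,348 events, 1,070 per arm.
- 60% against 54%: HR 0.847, 1,312 events, 1,151 per arm.

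So the stated 1,100 reproduces to within 3% as a log-rank calculation with 60% as the lower rate. The plan states neither the direction of the 6 points nor which of the two mortality endpoints they refer to.

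**Bias in the level, one arm.** With total mortality F and H = −ln(1 − F):

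- one minus Kaplan-Meier, other-cause deaths censored: 1 − exp(−(1 − q)H)
- cumulative incidence of cancer death: (1 − q)F

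At F = 0.60, H = −ln(0.40) = 0.9163. For q = 25%, 1 − exp(−0.75 × 0.9163) = 49.7%, against 0.75 × 60% = 45.0%.

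| Other-cause share q | 1 − KM | Cumulative incidence | Excess (points) |
|---|---|---|---|
| 10% | 56.2% | 54.0% | 2.2 |
| 20% | 52.0% | 48.0% | 4.0 |
| 25% | 49.7% | 45.0% | 4.7 |
| 30% | 47.3% | 42.0% | 5.3 |
| 40% | 42.3% | 36.0% | 6.3 |
| 50% | 36.8% | 30.0% | 6.8 |

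A coherence check at q = 25%: one minus Kaplan-Meier for other causes is 1 − exp(−0.25 × 0.9163) = 20.5%. Added to 49.7%, this makes 70.2%, although only 60% of patients have died.

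The excess shrinks quickly with lower mortality. At an illustrative F = 0.40 (H = 0.5108) it runs from 36.9% against 36.0% (0.9 points, q = 10%) to 22.5% against 20.0% (2.5 points, q = 50%).

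**Bias in the between-arm difference.** Take total mortality of 60% in one arm and 54% in the other, with the same other-cause hazard in both, so that the whole effect is on cancer death. The other-cause cumulative hazard is o = q × 0.9163. The cancer cumulative hazards are c0 = 0.9163 − o and c1 = 0.7765 − o, where 0.7765 = −ln(0.46). The Kaplan-Meier difference is exp(−c1) − exp(−c0). The cumulative incidence difference is 0.60 × c0/0.9163 − 0.54 × c1/0.7765.

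| q (60% arm) | Difference by 1 − KM | Difference by cumulative incidence | Shift (points) |
|---|---|---|---|
| 10% | 6.6 | 6.4 | 0.2 |
| 20% | 7.2 | 6.7 | 0.5 |
| 25% | 7.5 | 6.9 | 0.6 |
| 30% | 7.9 | 7.1 | 0.8 |
| 40% | 8.7 | 7.5 | 1.2 |
| 50% | 9.5 | 7.9 | 1.6 |

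The direction of the 6 points hardly matters. With 66% in the other arm, c1 = −ln(0.34) − o = 1.0788 − o, and its cumulative incidence is 0.66 × c1/1.0788. The shift is then 0.2 points at q = 10% (6.6 against 6.4) and 1.5 points at q = 50% (9.5 against 8.0). If the cause-specific hazards are equal in both arms, the shift is zero.

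**The case against.** The strongest reply is that the plan never says cancer-specific mortality goes through Kaplan-Meier with other-cause deaths censored. It speaks of survival data in general. The endpoint is mortality at a fixed time, and patients are to be followed for 5 years, so a simple proportion compared by chi-square would also fit the text. With complete follow-up that proportion equals the cumulative incidence. This stands as far as it goes: the Kaplan-Meier route is an inference, although the natural one for a mortality endpoint. It does not remove the point. The plan expects about 20% dropout, and a crude proportion needs a rule for incomplete follow-up that is not given. If both routes are open, a primary parameter has no fixed estimator.

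Second, the log-rank test is not at fault. With other-cause deaths censored it is a valid test of equal cause-specific hazards. Total mortality, the other primary parameter, has no competing event. Both statements are correct.

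Third, the eligibility criteria limit other-cause deaths by capping age and by excluding short life expectancy and, in the protocol, other malignancies. That is fair, but the documents do not turn it into a figure, so a range is all that can be shown.

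Fourth, the 10-year analysis starts follow-up at surgery, so its cumulative incidence curve can also be read at 5 years. That helps for the Danish and Swedish patients, but the post-trial analysis excludes Uruguay and does not settle how the trial's own 5-year figure is computed.

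**Conclusion.** The point holds as a should-fix. A primary cause-specific endpoint has no competing-risk estimator in the protocol or trial SAP. The only time-to-event estimator named would, on its natural reading, overstate absolute 5-year cancer mortality in each arm by about 2 to 7 points at 60% total mortality, or 0.9 to 2.5 points at 40%. These sizes rest on constant hazards and on an assumed 10% to 50% share of other-cause deaths. The between-arm difference moves by about 0.2 to 1.6 points when other-cause hazards are equal.

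A reader might go further in four ways that the documents do not support.

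- *That the bias is as large as the 6-point target difference.* The 6 points are a difference between arms, whereas the 2 to 7 points are an error in the level within an arm. That error has the same sign in both arms and largely cancels. Even the level error reaches 6 points only if about 36% or more of deaths are from other causes at 60% mortality.
- *That recurrence has the same fault.* The plan equates time to recurrence with recurrence-free survival and states no censoring rule for deaths. If death counts as an event, as that name suggests, Kaplan-Meier is appropriate.
- *That 3-year cancer mortality is now primary.* The amendment says only that 3-year results will be published too.
- *That the 10-year SAP prescribes Gray's test or a cause-specific log-rank test for cancer death.* It names neither. It assigns log-rank to overall mortality and gives Cox models as a sensitivity analysis.

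**What to change.** Under Statistical analysis and power, in both the protocol and the trial SAP:

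1. Restrict the Kaplan-Meier estimator to total mortality.
2. Estimate cancer-specific mortality at 5 years, and the 3-year figure that the amendment commits to publishing, with the cumulative incidence function, treating death from other causes as a competing event.
3. Report the between-arm risk differences with 95% confidence intervals, as section 6 of the post-trial SAP does.
4. If a log-rank test is kept for cancer death, state that it compares cause-specific hazards with other-cause deaths censored.

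The cost is a few sentences and a standard software option. No new data are needed beyond date and cause of death, which cancer-specific mortality already requires. The sample size is untouched.

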### **Randomisation and treatments**

Randomisation will take place by Internet from a central randomisation unit (appendix 12) placed at Department of Clinical Epidemiology in Århus Denmark. Randomisation will be stratified according to tumour stage and clinical centre. Randomisation will be blocked in variable groups of which the size will be kept secret for the participating centres. The allocation procedure should be concealed to the deliverers of treatment.

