### 4) *Endpoints*

The following endpoints will be analyzed:

- 10-year overall mortality rates and
- 10-year colorectal cancer-specific mortality rates.

The outcomes will be obtained from population-based cancer, death, pathology, and patient registries in Denmark and Sweden. We will exclude patients from Uruguay because we are unable to obtain adequate follow-up information from these patients.

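### The 5-year log-rank test names no strata although randomisation is stratified by stage and centre; stratifying by stage would gain about 1 to 5 points of power, and two sentences in the 10-year plan need clarifying

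*Combined protocol and SAP*

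**What the plan says.** Three parts of the combined document bear on this.

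- **Design.** Protocol, Randomisation and treatments: "Randomisation will be stratified according to tumour stage and clinical centre". The trial SAP (eStatistical Analysis Plan) names the same two factors and adds: "Randomisation will be blocked, in variable groups of 4 or 6".
- **5-year analysis.** Trial SAP, Statistical analysis and power: "Comparisons between groups will be made using the log-rank method". The protocol section of the same name also gives a log-rank test. Neither mentions strata, covariates or an adjusted model. A protocol amendment on efficacy parameters adds reporting at 3 years.
- **10-year analysis.** The post-trial SAP is a separate plan. Section 6 says: "The main analyses will be stratified by cancer stage and will be repeated for the subgroups of patients diagnosed with rectal and colon cancer". Its Cox model, a second sensitivity analysis, adjusts for stage but lists neither centre nor country. On country, section 6 says: "In the first sensitivity analysis, we will repeat the main analyses for trial participants from Denmark and Sweden". The next sentence is: "The overall and colorectal cancer-specific mortality rates will be compared between the 2 countries". Section 4 has already restricted the population: "We will exclude patients from Uruguay because we are unable to obtain adequate follow-up information from these patients".

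**The concern.** Stratified randomisation makes the arms alike on stage. An unstratified log-rank still counts between-stage variation in mortality as noise, although the design has removed its effect on the comparison of arms. The variance is then too large, the test rejects too seldom, and power paid for in the design is not collected. The trial looks for a 6-point difference, and the post-trial SAP calls the 5-year result not entirely conclusive, so a few points of power at no patient cost are worth having.

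In the 10-year plan the issue is wording. Stratifying the main analyses by stage may mean one test pooled across stages or a separate result for each stage. On the second reading there is no overall stage-stratified test. The country analysis can likewise be read as a repeat in the two countries pooled, which is the main population again, or as a repeat within each. A contrast of mortality between two countries is not randomised and says nothing about whether the effect of follow-up frequency differs between them.

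**Working it through.** **1. The plan's own figure.** Inputs from Statistical analysis and power: 5-year mortality 60%, difference 6 points, two-sided alpha 5% (the protocol states two-sided), power 85%, about 1,100 per group. The direction of the difference is not stated.

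Under proportional hazards HR = ln(1 − p2)/ln(1 − p1). Required events are 4(1.960 + 1.036)²/(ln HR)², and patients per arm are events/(2 × mean mortality).

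- 60% v 66%: HR = ln(0.34)/ln(0.40) = 1.177; 1,348 events; 1,348/(2 × 0.63) ≈ 1,070 per arm.
- 63% v 57%: HR 0.849; 1,338 events; about 1,115 per arm.
- 60% v 54%: HR = ln(0.46)/ln(0.40) = 0.8475; 1,312 events; 1,312/(2 × 0.57) ≈ 1,151 per arm. At 1,100 per arm there are 2,200 × 0.57 = 1,254 events, and power is 83.4%.

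So about 1,100 reproduces as a log-rank calculation. It allows nothing for stage.

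**2. What stratifying would change.** Simulated trials of 1,100 per arm had 24 centres (post-trial SAP, Study design), two stages, and blocks of 4 or 6 within stage by centre. Survival was exponential, censored at 5 years, with overall mortality 60% v 54%. Assumed, because the documents do not give them: a 50:50 stage mix, a stage III v II hazard ratio of 1.5 to 3, and a between-centre log-hazard SD of 0 or 0.2. The within-stage treatment HR (0.845 to 0.828) was set so that the overall difference stays at 6 points. As a check, with no stage or centre effect the unstratified test had 83.5% power (formula 83.4%) and 5.0% type I error.

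Power (%), 2,800 trials per row:

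| Stage HR | Centre SD | No strata | Stage | Stage × centre | Gain from stage | Change on adding centre |
|---|---|---|---|---|---|---|
| 1.5 | 0 | 83.5 | 84.4 | 83.8 | 0.9 | −0.6 |
| 2 | 0 | 84.7 | 87.0 | 86.6 | 2.3 | −0.4 |
| 2.5 | 0 | 85.6 | 88.8 | 88.5 | 3.2 | −0.3 |
| 3 | 0 | 87.2 | 92.2 | 91.6 | 5.0 | −0.6 |
| 2 | 0.2 | 84.5 | 86.8 | 86.7 | 2.3 | −0.1 |

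Type I error (%), nominal 5, Monte Carlo SE about 0.4:

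| Stage HR | Centre SD | No strata | Stage | Stage × centre |
|---|---|---|---|---|
| 1.5 | 0 | 5.61 | 5.39 | 5.25 |
| 2 | 0 | 4.86 | 5.29 | 5.32 |
| 2.5 | 0 | 3.43 | 4.79 | 5.14 |
| 3 | 0 | 3.68 | 5.25 | 5.39 |
| 2 | 0.2 | 4.04 | 4.86 | 5.29 |

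**3. A second simulation**, with 1,000 per arm and stage only, assumed stage II/III mortality of 50/70, 45/75 and 40/80%. These correspond to stage HRs of ln(0.30)/ln(0.50) = 1.74, ln(0.25)/ln(0.55) = 2.32 and ln(0.20)/ln(0.60) = 3.15. Power rose from 80.2 to 81.6, 81.2 to 85.1 and 84.7 to 90.1%, gains of 1.4, 3.9 and 5.4 points. Unstratified type I error was 4.5, 3.0 and 2.9%.

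**4. The country analysis.** The main 10-year analyses compare arms, so repeating them is also a comparison of arms. The population is already Denmark plus Sweden, so the repeat adds information only if done within each country. Centre was a randomisation stratum and each centre lies in one country, so that comparison is still randomised. The comparison of mortality between countries is not, and no treatment-by-country interaction is named.

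**The case against.** The strongest reply is that nothing here is invalid. An unstratified log-rank is a proper test of a randomised comparison, its error is on the safe side, and the plan nowhere says it will be unstratified; it is silent. The gain rests on assumed prognosis, is under 1 point at the weak end, and at 1,100 per arm leaves unstratified power at 83.5 to 87.2%, near the planned 85%. All of that stands. It makes this an efficiency and specification point, but gives no reason to forgo a free gain.

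Four stronger readings are tempting and are not supported.

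- **That the 10-year plan ignores the stratification factors.** It stratifies its main analyses by stage and puts stage in the Cox model. Only centre and country are absent.
- **That the first sensitivity analysis compares countries in place of arms, and so tests nothing.** Its first sentence repeats the between-arm analyses. With Uruguay already excluded, within each country is the natural reading. The comparison between countries is an addition. The repeat is redundant only if the two countries are pooled.
- **That omitting strata puts power below 85%.** A shortfall of that kind comes from the dropout arithmetic: 2,500 less 20% is 2,000, or 1,000 per arm, with log-rank power about 79.8% for 60% v 54%. That is a separate matter.
- **That leaving out centre costs power.** The simulations showed no gain from adding it.

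**Conclusion.** The point holds as a modest, correctable inefficiency in the 5-year plan and two ambiguities in the 10-year plan. The documents stratify randomisation by stage and centre and name no strata for the 5-year test. Stratifying that test by stage would add about 1 to 5 points of power for an assumed stage HR of about 1.5 to 3 and an even stage mix. The gain would be smaller if stage were less prognostic.

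The unstratified test is not biased. Its type I error fell to about 3.4 to 3.7% at stage HRs of 2.5 and 3, but showed no conservatism at 1.5 (5.6%, SE about 0.4), so the conservatism should be claimed only where stage is strongly prognostic.

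For the 10-year plan the conclusion rests on wording alone. The form of the stage stratification and the unit of the country analysis are not stated, and on either reading nothing planned formally tests whether the effect is the same in the two countries.

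**What to change.** **Trial SAP and protocol.** Make the primary 3- and 5-year test a log-rank pooled across the stage strata used at randomisation, and take the hazard ratio from a Cox model stratified the same way. State that stage means the value entered at randomisation, since final postoperative staging is also collected. Country, or centre with small centres pooled, may be added as a design factor, but no power gain should be claimed for it.

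**Post-trial SAP, section 6.** State that the stage-stratified main analysis includes one combined test across stages, whether or not stage-specific results are also shown. State that the first sensitivity analysis estimates the difference between arms within Denmark and within Sweden, with 95% confidence intervals, and add a treatment-by-country interaction test. Keep the comparison of mortality between countries, if wanted, as description only.

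**Cost.** A few sentences and minor code. Stage and centre had to be known to randomise, and country follows from centre. No new data or patients are needed.
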